## Abstract

**Introduction:**

Spirometry is a point-of-care lung function test that helps support the diagnosis and monitoring of chronic lung disease. The quality and interpretation accuracy of spirometry is variable in primary care. This study aims to evaluate whether artificial intelligence (AI) decision support software improves the performance of primary care clinicians in the interpretation of spirometry, against reference standard (expert interpretation).

**Methods and analysis:**

A parallel, two-group, statistician-blinded, randomised controlled trial of primary care clinicians in the UK, who refer for, or interpret, spirometry. People with specialist training in respiratory medicine to consultant level were excluded. A minimum target of 228 primary care clinician participants will be randomised with a 1:1 allocation to assess fifty de-identified, real-world patient spirometry sessions through an online platform either with (intervention group) or without (control group) AI decision support software report. Outcomes will cover primary care clinicians’ spirometry interpretation performance including measures of technical quality assessment, spirometry pattern recognition and diagnostic prediction, compared with reference standard. Clinicians’ self-rated confidence in spirometry interpretation will also be evaluated. The primary outcome is the proportion of the 50 spirometry sessions where the participant’s preferred diagnosis matches the reference diagnosis. Unpaired t-tests and analysis of covariance will be used to estimate the difference in primary outcome between intervention and control groups.

**Ethics and dissemination:**

This study has been reviewed and given favourable opinion by Health Research Authority Wales (reference: 22/HRA/5023). Results will be submitted for publication in peer-reviewed journals, presented at relevant national and international conferences, disseminated through social media, patient and public routes and directly shared with stakeholders.

**Trial registration number:**

NCT05933694.

STRENGTHS AND LIMITATIONS OF THIS STUDYReal-world spirometry traces completed in primary care, irrespective of technical quality, will be used.To replicate real-world primary care in the UK, study participants will not be limited to general practitioners, but will include other members of multidisciplinary team that are expected to perform or/and interpret spirometry in primary care.The trial will be advertised and recruited nationally to maximise participation and variation in participant sample.The trial statistician will be blinded to group allocation.Trial outcomes will include all relevant aspects of spirometry interpretation, including assessment of technical quality, pattern recognition and diagnosis prediction.

## Introduction

Chronic respiratory disease has significant negative impact on quality of life and is the third leading cause of death globally, and one of the highest contributors to economic burden for healthcare systems.^1^ Chronic obstructive pulmonary disease (COPD) alone accounted for 3.3 million deaths worldwide in 2019, increasing 14% over the previous 10 years.^2^ Accurate and timely diagnosis of respiratory disease is key to improving access to treatment and patient outcomes, and long delays to diagnosis for individuals with chronic lung diseases are well documented.^3–5^

Spirometry is a simple, point-of-care lung function procedure recommended to support the diagnosis and monitoring of COPD and asthma, the most common long-term respiratory conditions.^6 7^ In many western and low/middle-income countries, spirometry will be performed and interpreted in non-specialist respiratory settings. However, there is inequity in spirometry provision in primary care and community settings; historical challenges with quality, skills and competence in interpretation, and funding, have been compounded by the COVID-19 pandemic.^8^ Spirometry performed in primary care and community settings has been shown to not meet international criteria in over 85% of cases.^9^ A low level of confidence in assessing spirometry quality is also common among general practitioners (GPs).^10^ Improving prevention and early diagnosis has been identified as a priority in the Global Impact of Respiratory Disease report.^11^ In practice, this requires improved equity, access and quality of spirometry provision.

Recent work has shown that artificial intelligence (AI)-powered decision support software can provide automated technical quality assessment and interpretation of full lung function tests.^12 13^ This software can outperform pulmonologists in diagnostic prediction from lung function tests.^13^ Similar AI software that interprets spirometry (usually the only lung function test accessible in many healthcare settings) may be particularly helpful in primary care to support clinicians who have generalist roles and less experience in respiratory diagnosis. Qualitative work highlighted that validation and evaluation of the effectiveness of AI software is key in engaging clinicians and commissioners to have confidence in implementation in clinical practice.^8^

The primary objective of this study is to compare the performance of primary care clinicians in the interpretation of 50 real-world spirometry records with or without AI spirometry decision support software reports.

## Methods and analysis

### Trial design and registration

This is a parallel, two group, randomised controlled, statistician-blinded efficacy trial to evaluate whether AI spirometry decision support software can improve the performance of primary care clinicians in their interpretation of real-world spirometry. Each clinician will be provided with the same clinical dataset of 50 de-identified, real-world patient spirometry records through an online platform (Qualtrics XM), and asked to answer questions about preferred diagnosis (ie, diagnosis they think is most likely) and differential diagnosis (ie, second most likely diagnosis) based on spirometry and limited clinical data, the technical quality of spirometry and the spirometry pattern. Questions will also explore clinicians’ confidence in their assessments.

Participants will be allocated at random to receive either spirometry records alone or spirometry records with the addition of the AI software report. The clinical spirometry records will be de-identified (name, date of birth, address, postcode, occupation, GP, medications data removed), by a member of the clinical care team.

Royal Brompton and Harefield Hospitals (RBHH), Guy’s and St Thomas’ NHS Foundation Trust (GSTFT) will act as study sponsor. This study has been reviewed and given favourable opinion by Health Research Authority (HRA) Wales (reference: 22/HRA/5023).

### Study population

Potential participants will be clinicians working in primary care involved in spirometry referral and interpretation.

#### Eligibility criteria

Eligibility criteria will be: (1) a clinician working in primary care (defined as >50% of job plan in primary care) in the UK who refers for or performs spirometry (typically GP, practice nurse); (2) able to access an online study platform in order to review spirometry sessions; (3) able to provide informed consent via the study platform.

Exclusion criterion will be: (1) clinicians who have completed specialist training in respiratory medicine and are recognised by the General Medical Council with the right to practise as a consultant in respiratory medicine in the National Health Service.

Eligibility criteria will be used as screening questions on the online study platform prior to participants being able to consent to participate.

Participants will be randomised 1:1 to either control (report 50 spirometry records alone) or intervention (report same 50 spirometry records with access to an AI spirometry interpretation report for each spirometry result). Randomisation will be done by the study online platform at the point of consent to the study by minimising according to job role (GP: yes or no) and spirometry accreditation from the Association for Respiratory Technology and Physiology (performance only, interpretation only, performance and interpretation, no accreditation) and then randomising by a random number generation algorithm performed by the online platform.

### Recruitment and consent

Recruitment to the study will be advertised through national and local primary care networks, professional networks, the institution website and social media will be used. By advertising and recruiting nationally, the recruitment strategy aims to engage with clinicians from diverse backgrounds in terms of the patient population they serve, age, years of clinical experience, job role and ethnicity. We will offer financial reimbursement for all potential participants participating and completing the study, which may attract some who might not be interested in AI or respiratory diagnostics.

Clinicians will be sent a letter outlining the research study with the option for them to express interest in participating. The letter serves as the participant information sheet (see online supplemental information) and will be sent via email. Participants who express interest in taking part will be sent a link to the online study platform where they will be able to complete the eligibility screening questions and, if applicable, consent form online. The study will also be advertised on the RBHH research website with a link available to the online study platform. Participants will be able to withdraw without giving any reason, and the number of participants registering but not completing the study will be recorded. Randomisation will be kept concealed until the point of the allocation of the participant to a study arm.

10.1136/bmjopen-2024-086736.supp1Supplementary data

### Setting

The study will be conducted via an online platform (Qualtrics XM).

### Procedure

Study participants (participating clinicians) will independently assess the same 50 spirometry records, in the same order, through a bespoke designed online platform developed using Qualtrics XM (Seattle, USA). Participants will be blinded to the reference standards. See figure 1 for example. The patient spirometry records were randomly selected from a database comprising 1122 patients undergoing spirometry in primary care and community-based respiratory clinics in Hillingdon borough between 2015 and 2019. An online randomiser will be used to select the 50 spirometry sessions used in the trial (https://www.randomizer.org/), according to ‘disease category’ so that of the 50 spirometry traces selected, 40% will be from patients with COPD, 20% will have normal spirometry and 10% for each of the four other disease categories (asthma, interstitial lung disease (ILD), other obstructive, other disease/unidentifiable category), to represent a likely distribution of diagnoses in a primary care setting.

**Figure 1 F1:**
[figure not shown]
Example spirometry case and questions for primary care clinicians. FEV_1_, forced expiratory volume in 1 s; FVC, forced vital capacity.

For each spirometry record, the primary care clinician participant will answer the following questions on the Qualtrics platform:

What is the technical quality of the spirometry? (a drop-down box containing the options: acceptable (quality grade A or B), not acceptable). Technical quality will be defined according to the ATS/ERS 2019 Spirometry Technical Statement, provided to participants via a link embedded in the online platform.One response for forced expiratory volume in 1 second (FEV_1_) and one question for forced vital capacity (FVC).How confident are you in your technical quality assessment using a visual analogue scale (0: not confident at all to 10: very confident)?Provide a pattern interpretation based on spirometry report received. Options: normal, airflow obstruction, possible restriction or non-specific pattern, possible mixed disorder.How confident are you in your pattern interpretation using a visual analogue scale (0: not confident at all to 10: very confident)?Provide a preferred diagnosis based on spirometry report received and information (a drop-down box containing the options: asthma, COPD, ILD, normal lung function, other obstructive disease and other unidentifiable disease): **preferred diagnosis**.Provide a differential diagnosis based on spirometry report received and information (a drop-down box containing the options: asthma, COPD, ILD, normal lung function, other obstructive disease and other unidentifiable disease): **differential diagnosis**. The previously chosen ‘preferred diagnosis’ is automatically removed from the list of available options.How confident are you in your diagnosis using a visual analogue scale (0: not confident at all to 10: very confident).

Participants will have 8 weeks to review the 50 spirometry traces; reminders will be sent at weeks 3, 6 and 7 to those who have not completed their assessments (figure 2).

**Figure 2 F2:**
[figure not shown]
Study schedule. ARTP, Association for Respiratory Technology and Physiology; GP, general practitioner.

### Intervention: AI spirometry software

The AI software was developed by ArtiQ (Leuven, Belgium), and provides AI-supported quality assessment and interpretation guidance of spirometry sessions (online supplemental file). The quality assessment component leverages deep learning methods to perform the subjective assessment of spirometry quality assessment (ie, related to curve shape), as well as implementing the objective criteria from international guidance (ie, related to numeric criteria). The AI component of the software mimics the subjective visual inspection of data usually performed by technicians. Per session it provides an overall session quality grade according to ATS/ERS 2019 Spirometry Technical Statement (A–F) and calculates the best trial (spirometry trace) which should be considered for diagnostic interpretation. The model was trained based on spirometry measurements from the National Health and Nutritional Examination Survey (NHANES 2011–2012)^12^ and validated in clinical trial settings.^14^

The spirometry interpretation component is a decision support software focusing on the diagnostic interpretation of spirometry sessions. It provides support in pattern interpretation according to international interpretation guidelines (ie, normal, obstructive and/or restrictive)^15^ and a disease probability. The disease probability model was originally trained to distinguish eight of the most common categories (seven diseases+normal lung function) detectable with full pulmonary function testing.^13^ For use in primary care settings, the model has been adapted to identify six categories—asthma, COPD, ILD, normal lung function, other obstructive disease (such as cystic fibrosis and bronchiectasis) and other unidentifiable disease—solely based on spirometry using the same training set. The rationale for reducing the number of categories to identify is based on the reduced lung function dataset available when working in a primary care environment compared with a hospital-based pulmonary function testing laboratory. The categories selected are those most commonly found in primary care, with spirometry testing indicated mainly in COPD and asthma diagnosis.

When the quality model identifies the data quality of the spirometry session to be poor (ie, quality of FEV_1_ and/or FVC is not A or B according to ATS/ERS 2019 guidelines), the following disclaimer is added to the interpretation report: ‘Data quality is not sufficient. Interpretation above might not represent the patient’s lung function’. Participants will still be asked for a diagnosis and spirometry interpretation despite the bad quality.

### Reference standard

Reference standards for diagnosis for the 50 spirometry traces were defined before commencement of the trial, by two pulmonologists. Primary and secondary care medical records were reviewed independently by two pulmonologists from the RBHH, UK. The diagnostic reference standard was attributed to one of six categories (COPD, asthma, ILD, other obstructive disease, normal, other) by each pulmonologist. In participants with multiple respiratory diagnoses (eg, COPD and ILD), the pulmonologist was asked to choose, to the best of their abilities, the predominant category. If consensus could not be reached between the two pulmonologists, these cases and their medical records were reviewed by a third pulmonologist to adjudicate independently. All pulmonologists ([name], [name], [name]) were accredited specialists in respiratory medicine with a minimum of 8 years as a consultant in the National Health Service, with expertise in the diagnosis and management of COPD and other chronic respiratory diseases. Pulmonologists had no access to the AI software reports, nor had any communication with the software engineer or software company.

Reference standards for the technical and pattern interpretation were completed by a respiratory physiologist ([name]) with 26 years experience. The respiratory physiologist was asked to rate the technical quality of the FEV_1_ and FVC using the categories acceptable (quality grade A and B ATS/ERS 2019 guidelines) or not acceptable (quality grade C, D, E, F, U).^15^ For pattern interpretation of the spirometry, the respiratory physiologist was asked to choose from the following four categories: normal, airflow obstruction, possible restriction or non-specific pattern, possible mixed disorder.

All pulmonologists and respiratory physiologist were blinded to AI software reports.

### Study outcomes

The primary endpoint for a primary care clinician participant is the performance of their preferred diagnosis, defined to be the number of correct cases identified expressed as a percentage out of the total number of spirometry records. A correct case is where the participant’s preferred diagnosis matches the reference final diagnosis (described earlier). The secondary endpoints, expressed per participant are listed in table 1.

**Table 1 T1:** Secondary endpoints

Secondary endpoints	Definition	Measured	Reference standard
Quality assessment of the spirometry trace	A correct case is where the participant’s quality grade matches the reference quality grade. Units will be percentage of total cases that are correct	Multiple choice categories: acceptable (grade A/B) or not acceptable (grades C/D/E/F/U)	Respiratory physiologist
Quality assessment self-rated confidence		Visual analogue scale (0–10) where is 0=not confident at all; 10=very confident	
Pattern interpretation of the trace	A correct case is where the participants’ selected pattern matches the reference pattern. Units will be percentage of total cases that are correct	Multiple choice categories: normal, airflow obstruction, possible restriction or non-specific pattern, possible mixed disorder	Respiratory physiologist
Pattern interpretation self-rated confidence		Visual analogue scale (0–10) where is 0=not confident at all; 10=very confident	
Differential diagnostic performance	A correct case is where the preferred or differential diagnosis matches the reference final diagnosis. Units will be percentage of total cases that are correct	Multiple choice categories: asthma, chronic obstructive pulmonary disease, interstitial lung disease, normal lung function, other obstructive disease and other unidentifiable disease	Pulmonologist
Diagnostic self-rated confidence		Visual analogue scale (0–10) where is 0=not confident at all; 10=very confident	

### Sample size calculation

The sample size calculation was informed by previous feasibility data from 30 primary care practitioners assessing five spirometry traces. The preferred diagnosis matched the reference diagnosis in a mean (SD) of 55% (19%) of spirometry records. We have assumed the same SD of 19%, which is conservative because more cases will be assessed per practitioner, leading to less variable practitioner rates. As the calculation involves conservative assumptions, the power was set below 90%, to be 85%. With 132 participants (66 per group) this allows for detection of a 10% difference (a mean of 5 extra cases in 50) in the rate of cases correctly identified to match the reference standard (mean 65% vs mean 55%) using an unpaired t-test at the two-sided 5% significance level.

The recruitment target was originally estimated at 156 practitioners to allow for an estimated 15% drop out. However, a preliminary analysis of completion rate of the first 50 recruited participants demonstrated that 29 of the 50 participants scored all 50 spirometry records within the 8-week study period (58% completion). Based on this data, the study statistician advised increasing the recruitment target to 228 to account for 42% non-completion (see the Amendment section).

Descriptive statistics will be performed for demographics, baseline characteristics and endpoint data: number and percentage for categorical data and mean and SD or median and interquartile range (IQR) for non-normally distributed continuous data.

### Statistical analysis

Survey responses from participants will be collated in a secured, online database. A Statistical Analysis Plan will be developed and statistical analysis will be conducted by the study statistician. The statistician will be blinded to control/intervention group allocation. Descriptive statistics will be presented for demographic, baseline characteristics and endpoint data. Number and percentage will be presented for categorical data. Mean and SD will be presented for normally distributed continuous data while median IQR will be presented for non-normally distributed continuous data.

The number of participants consented, randomised, and completing the study will be described in a study Consolidated Standards of Reporting Trials diagram.

Data analysis will be performed on an intention to treat basis. Data will be analysed with the statistical software Stata V.17.0. All statistical tests will be two-sided and significance set at p<0.05.

#### Primary endpoint analysis

For each participant, diagnostic performance will be calculated as percentage of the 50 spirometry procedures where the final diagnosis was correctly identified. In each randomised group, the diagnostic performance will be summarised as the mean of the participants’ diagnostic performance. A two-sample unpaired t-test will be used to assess the mean difference in correct response between the two randomised groups. The assumptions for the two-sample t-test will be tested and where the assumption for equal variances fails then the Welch t-test will be used.

Randomisation will be stratified according to job role (GP: yes or no) and Accreditation from Association for Respiratory Technology and Physiology (performance only, interpretation only, performance and interpretation, no accreditation), therefore an analysis of covariance will be used to compare the intervention and control groups by adjusting for the main effects of the stratified variables. To internally validate the estimate of the difference between the two groups bootstrap estimation of difference will be done by taking 100 from the analysis of covariance model or Welch's t-test.

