#### Missing data

Only participants who complete at least 70% of the spirometry cases will be included in the primary analysis. We will compare the baseline characteristics and demographics of those who completed <70% of questions with those who completed ≥70% of questions to identify any systematic differences between completers and non-completers.

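### The primary endpoint divides by all 50 records but admits clinicians who answered as few as 35, so as written the score mixes accuracy with completion

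*Protocol article*

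**What the plan says.** The denominator is given three times in the protocol article, always as the full set:

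- Abstract, Methods and analysis: "The primary outcome is the proportion of the 50 spirometry sessions where the participant’s preferred diagnosis matches the reference diagnosis".
- Study outcomes: the endpoint is "the number of correct cases identified expressed as a percentage out of the total number of spirometry records".
- Primary endpoint analysis: "diagnostic performance will be calculated as percentage of the 50 spirometry procedures where the final diagnosis was correctly identified".

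Study outcomes also defines a success: "A correct case is where the participant’s preferred diagnosis matches the reference final diagnosis".

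The Missing data section sets who is analysed: "Only participants who complete at least 70% of the spirometry cases will be included in the primary analysis". It gives no other denominator for those who answered some but not all cases, and no rule for a blank.

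Two further facts bear on this. Under Procedure, participants "independently assess the same 50 spirometry records, in the same order". Under Sample size calculation, 29 of the first 50 recruits finished all 50 records in the 8-week window. The article does not say how far the other 21 got.

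**The concern.** The two rules do not fit together. If a blank is meant to count as incorrect, every randomised clinician has a score out of 50 and no 70% threshold is needed. If the threshold is there to ensure enough answers to measure accuracy, a fixed denominator of 50 defeats it.

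Followed literally, up to 15 unanswered cases per analysed clinician count against them. A difference between arms in how many cases are finished would then appear as a difference in diagnostic accuracy. Such a difference is plausible, because only the intervention arm has an extra report to read with each case, which could speed up or slow down completion. The secondary percentage endpoints in Table 1 are also defined on total cases and are to be analysed in the same way.

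**Working it through.** **The plan's own figures.** Inputs from Sample size calculation: difference 10 points (65% versus 55%), SD 19, two-sided 5%, power 85%. The normal approximation gives n per arm = 2 × (1.960 + 1.036)² × (19/10)² ≈ 64.8, so 65. The exact t-test gives 65.8, so 66 per arm and 132 in total, with power 85.1%. Recruitment: 132/0.85 = 155.3, so 156; 132/0.58 = 227.6, so 228. All are reproduced and are not in dispute.

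**Inclusion threshold.** 0.70 × 50 = 35, so analysed partial completers have 35 to 49 answers.

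**Effect on one clinician.** Expected score = accuracy × answered/50.

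| Answered | 55% accuracy | 65% accuracy | Difference |
|---|---|---|---|
| 35 | 38.5 | 45.5 | 7.0 |
| 40 | 44.0 | 52.0 | 8.0 |
| 45 | 49.5 | 58.5 | 9.0 |
| 49 | 53.9 | 63.7 | 9.8 |
| 50 | 55.0 | 65.0 | 10.0 |

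**How many are affected.** Not stated. If 5, 10 or all 21 of the early non-finishers reached 35 cases, partial completers would be 5/34 = 15%, 10/39 = 26% or 21/50 = 42% of those analysed.

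**Effect on the arm comparison.** The partial-completion rates here are assumptions.

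- Equal rates, 20% of each arm at 35 answers: 10 × (1 − 0.20 × 0.30) = 9.4 points, a mild dilution.
- No true effect, 20% of one arm only at 35 answers: 0.20 × 0.30 × 55 = 3.3 spurious points, against whichever arm stops early.
- No true effect, 21% versus 10% partial completers, answers spread evenly over 35 to 49 (mean 42, so 8 missing): 0.11 × 8/50 × 55 = 0.97 points. A simulation with these rates, identical ability and drop-out unrelated to ability gave 0.86 when dividing by 50, −0.04 when dividing by cases answered and 0.00 with adjustment for each case.
- No true effect, 10% (control) versus 30% (intervention), answers uniform on 35 to 49, 66 per arm, 4,000 simulated trials: −1.7 points and 8.1% rejection when dividing by 50, against 0.0 points and 5.4% when dividing by cases answered.

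**Effect on the SD.** Let r = answered/50, with 20% partial completers uniform on 35 to 49. Then E(r) = 0.8 + 0.2 × 0.84 = 0.968 and E(r²) = 0.8 + 0.2 × 0.713 = 0.9426. With mean 55 and SD 19, the variance of the score is 0.9426 × (19² + 55²) − (0.968 × 55)² ≈ 357, so the SD is about 18.9, essentially unchanged.

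**The case against.** The strongest reply is that the article never says in words that a blank is wrong. The three definitions can be read as describing someone who assesses the whole set, and the article says a Statistical Analysis Plan will be developed. Counting missing as incorrect is also a recognised choice that suits the intention-to-treat statement. It is true that the scoring is inferred. However, it follows directly from the stated formula and the stated inclusion rule, so it concerns what the protocol fixes and not a detail it leaves open. If missing-as-incorrect were intended, excluding people below 70% would not follow from it.

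The reply is also right about size. With SD 19 and 66 per arm the standard error of the difference is 19 × √(2/66) ≈ 3.3 points, so a 0.9-point bias is about a quarter of one standard error. Even that needs an assumed imbalance, and reversing the imbalance reverses the sign. Nor does a loss of power follow: 228 × 0.58 ≈ 132 full completers are already planned for, and partial completers come on top of them.

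Three stronger readings are tempting but not supported:

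- A reader might infer that low-scoring partial completers inflate the SD. At the planning SD they do not. A modest rise would need a smaller true SD: about 12.2 to 12.5 if it were 12, or at most 13.4 if all stopped at 35.
- A reader might infer that the missing cases must be the last ones. The order is fixed, but the article does not say that cases cannot be skipped, nor how diagnoses fall along the order.
- A reader might infer that the t-test and analysis of covariance must give way to a case-level model. In the simulation the answered-case denominator alone already removed the bias.

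**Conclusion.** The point holds. Read together, the fixed denominator of 50 and the 70% inclusion rule make the primary endpoint a mixture of accuracy and completion for anyone with 35 to 49 answers. Equal partial completion slightly dilutes the effect, and unequal completion biases it in either direction. The actual size cannot be stated without completion counts by arm. The 0.9-point and 3.3-point figures are scenarios that rest on assumed rates, a common accuracy of about 55% and drop-out unrelated to ability. The defect is in the definition and does not depend on those scenarios.

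Dividing by answered cases restores the planned scale only if accuracy is the same on answered and unanswered cases. Because the order is fixed, early stoppers may miss the same later cases, so this assumption deserves a check.

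**What to change.** Before unblinding, state that for participants with 35 to 49 answered cases the primary endpoint and the secondary percentage endpoints are calculated over the cases answered. Keep the planned t-test and analysis of covariance. Add two labelled sensitivity analyses:

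- percentage of 50, with unanswered counted as incorrect;
- a case-level model with a term for each case, so that clinicians who stopped early are compared on the same traces.

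Report the number with 35 to 49 answers by arm. In the Missing data section, use one unit for the 70% threshold, which is currently expressed both in cases and in questions. The cost is a change of analysis wording and two extra analyses; no new data are needed.
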